| 5. Purpose of the study | The haemodynamic management of patients undergoing liver resections by anaesthesiology is determined by the goal to minimize the intraoperative bleeding during the surgical incision of the liver . This goal is reached by a hypovolaemic volume and fluid strategy to reach a low central-venous pressure. Thereby the backwards flow of the blood from the right heart by the liver veins to the resection surface of the liver is minimized and the blood loss will be reduced. This management is constituted by studies of the 1990ies as a possibility to reduce perioperative morbidity and mortality .  In recent years the surgical patient population changed due to a higher number of comorbidities especially of cardiovascular diseases. According to our clinical experiences this implies that some patients show a substantial drop of stroke volume and cardiac output with consecutive decreased perfusion especially of the splanchnic area induced by this restrictive fluid and volume therapy.  With the oesophageal Doppler and the LiDCOrapid there are two minimal-invasive monitors to offer valid measurements of stroke volume and therefore offer the possibility to guide volume and catecholamine therapy. In colorectal and gynaecological-urological resections and in traumatology the benefit of advanced monitoring on hospital length of stay is well documented in the literature (table of studies in appendix 1). But these studies direct on an intraoperative optimization of cardiac preload according to the Frank-Starling mechanism. For liver resections this approach is not feasible due to the increased risk of intraoperative bleeding. Therefore we created an algorithm for a restrictive volume management by maintaining cardiac output and splanchnic perfusion without preload optimization during the course of surgery. According to our knowledge up to date there is no algorithm in the literature for a goal-directed, restrictive volume management during liver surgery.  The goal of this study is to compare the developed intraoperative, restrictive, goal-directed volume protocol based on advanced haemodynamic monitoring versus standard of care to evaluate the impact on stroke volume as primary outcome measure and to further evaluate the impact on the influence on surgical proceedings and postoperative parameters as secondary outcome measures.  A further goal of this study is with the collaborations of the colleagues of the clinic of general, visceral and transplantation surgery to describe the particular perioperative modules and by their standardization to increase the quality and transparency of the study results. |

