| 27. If applicable: Methods to detect, document and communicate adverse events (when, with whom and how??) | The patients will be supervised intensively during the operation by the anaesthetist and can only leave the operation area when the discharge criteria are fulfilled in the recovery room.  Apart from the routine daily care delivered by the physicians in the departments of General, Visceral and Transplantation Surgery, there will also be a visit from the study physicians of the Anaesthesiology department, so that adverse events can be detected.  The occurrence of adverse events should be communicated to the study director within 24 hours.  A liver resection represents a surgical intervention with increased risk and deviation of parameter frequently occurs. Due to that fact a list of exceptions will be generated because the deviations of the values are related to the surgical intervention and are not indicative of an adverse event induced by the study protocol. For the values of perioperative blood samples a plausibility list will be generated which regulates the limits the pathological values from the reportable events.  Post-operative monitoring will continue until the day of hospital discharge or the 8th post-operative day, whichever is earlier. |
| 28. Procedures to ensure the secrecy of stored data, documents and, if applicable, samples. State how the encoding of patient data occurs *(please don’t use patient initials and birthdays as coding schemes!)* | A pseudonym is generated for every patient and the list of pseudonyms is kept locked away. Patient documentation is only done using the pseudonym.  The pseudonym will be formed from the first two letters of the study name followed by the number of the center CVK=1, CCM=2, followed by a three digits incrementally rising number.  As an example for the first patient of the study:  LE 1 001 |

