**Appendix 3:**

**Algorithm for the goal-directed volume and catecholamine therapy of the intervention groups**

*: The stroke volume after the initial preload-optimization is the Starting-SVI.

#: The drop of the stroke volume index is related to the Starting-SVI.

x: Are there clinical (a opinion of the surgeon in combination with the estimation of the anaesthesists) or haemodynamically (in the form of an elevated central-venous pressure in combination with the clinical estimation) sign for a backward failure of the right ventricle to the liver, the administration of enoximone (initial dosis: 2,5µg/kg/min, can be increased up to 10µg/kg/min or a bolus administration of 1µg/kg) or nitroglycerine should be indicated according to the clinical estimation of the anaesthesists in charge. The simultaneous administration of both drugs must not be indicated in the same patient due to the risk of hypotension.

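### Item 27 attributes listed deviations to surgery in advance, so effects of the fluid and catecholamine algorithm on those values could be left out of adverse-event reporting

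*Protocol*

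**What the plan says.** Item 27 of the protocol describes how adverse events are found and passed on. Besides routine care, "there will also be a visit from the study physicians of the Anaesthesiology department, so that adverse events can be detected". The general rule is "The occurrence of adverse events should be communicated to the study director within 24 hours".

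The item then observes that liver resection is a higher-risk operation in which abnormal parameters are common, and continues: "Due to that fact a list of exceptions will be generated". The reason it gives is that "the deviations of the values are related to the surgical intervention and are not indicative of an adverse event induced by the study protocol". A second list covers laboratory results: "For the values of perioperative blood samples a plausibility list will be generated which regulates the limits the pathological values from the reportable events".

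Neither list is in the document. For listed items, item 27 states no case-by-case judgement of cause and no way to override the list.

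Item 13 allows the whole study to be stopped if the study leader decides that the risks have become untenable.

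**The concern.** A list of expected perioperative deviations is ordinary and useful. The difficulty is the reason attached to this one. It treats every listed deviation as surgical in origin and not due to the protocol, whichever arm the patient is in.

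In this trial the protocol-specified treatment is a scheme for giving volume and vasoactive drugs. Circulatory and laboratory values are what such a scheme changes, for better or worse. If it worsened a listed value, the rule would class the change as surgical, and the event need not reach the study director. At stake is the one route described in item 27 by which possible harm from the algorithm reaches the person in charge while patients are still being enrolled.

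**Working it through.** No arithmetic applies: the protocol gives no adverse-event rate, and the point rests on no figure. The check sets the relevant parts of the protocol side by side.

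1. **What the rule decides.** Item 27 gives cause as the ground for the exception ("the deviations of the values are related to the surgical intervention and are not indicative of an adverse event induced by the study protocol"). The sentence can be read in two ways: listed deviations are not adverse events at all, or they are adverse events not caused by the protocol. Either way, a list of exceptions placed directly after the 24-hour rule reads most naturally as an exception to that rule. The laboratory list likewise separates abnormal values from reportable ones.

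2. **What the intervention acts on.** Item 10 and Appendix 3 have the algorithm guide volume and catecholamines. Both intervention groups start with a gelatin bolus, repeated according to the stroke-volume response; Appendix 3 calls this step initial preload optimisation. Blood-pressure and cardiac-index targets follow until the resection ends, and preload optimisation is then resumed.

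3. **Whether the protocol itself expects the algorithm to move such values.** It does. The primary hypothesis in item 4 concerns stroke volume. The secondary hypotheses and outcomes extend to blood loss, organ dysfunction and postoperative liver function, the last measured partly by laboratory tests. A plan that tests whether the algorithm changes these values cannot also assume that it plays no part when a listed one is abnormal.

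4. **What the protocol says about direction.** Two statements show awareness that volume and drug treatment can do harm. On the preload optimisation used in other kinds of surgery, item 5 says: "For liver resections this approach is not feasible due to the increased risk of intraoperative bleeding". Appendix 3 says that simultaneous use of two named drugs "must not be indicated in the same patient due to the risk of hypotension". Neither states a risk of the algorithm as a whole: the first explains why preload is not optimised throughout surgery, and the second is a safeguard against one combination. They show only that bleeding and hypotension are recognised as possible consequences of treatment, not of surgery alone.

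5. **What could separate the two causes.** All three arms undergo liver resection. A deviation in one patient does not show whether surgery or the algorithm produced it; a difference in frequency between arms could. That requires listed deviations to be recorded in every arm without a prior attribution.

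6. **What is protected anyway.** Item 4 makes haemodynamic parameters, blood loss, organ dysfunctions, infections and liver-function laboratory tests secondary outcomes. Item 15 tests secondary endpoints with Fisher's exact or Mann-Whitney tests. These comparisons do not depend on whether a value was also called an adverse event.

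7. **What remains exposed.** Two things: reporting of listed deviations to the study director during the trial, and any exempted value that is not also a secondary outcome. The second group cannot be named without the lists.

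**The case against.** The strongest reply is that the main foreseeable harms are trial endpoints. A reader might infer from item 27 that harm from the algorithm would never be compared between arms. The documents do not support that: items 4 and 15 provide for the comparison of the outcomes in step 6. A table of adverse events by arm may also stand in an analysis plan that is not shown, so its absence is not a fault. This reply stands and limits the point. It does not remove it, because an endpoint analysis does not replace the adverse-event report item 27 provides for during the trial.

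The exemption is also narrow. It concerns deviations of parameters and blood values. Clinical events are not stated to be exempt, adverse events not on the lists stay under the 24-hour rule, and study physicians visit in addition to routine care. Item 13 also lets a patient be withdrawn in the patient's best interests, and does not confine the study leader's decision to item 27 reports. All of this stands.

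A reader might further infer that the lists could be drawn up after events were seen, by people who knew the arm. The protocol does not say so. Future tense is natural in a prospective application, item 19 says that study staff are not the treating doctors, and item 23 places unblinding after the last patient's last visit. Fixing the lists before enrolment is a precaution, not an answer to a demonstrated fault.

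Finally, a reader might try to size the defect from the 20 patients per arm. What an arm of that size can exclude is the same with or without an exception list, so it does not measure this problem.

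**Conclusion.** The point holds in limited form. Item 27 states a causal presumption that the design does not justify: the algorithm acts on the same kinds of values as the lists, and surgery is common to all arms. Deviations caused by the algorithm could therefore be left out of adverse-event reporting to the study director. It does not follow that harm in general goes unreported, or that the main harms go uncompared.

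No numerical size can be given, because neither list's contents nor any event rate is stated. The conclusion rests on three assumptions: that the lists will include values volume or vasoactive treatment can change, which the wording makes likely but does not prove; that listed items are meant to be excepted from the reporting rule; and that the study director of item 27 and the study leader of item 13 are the same role. This is a modest safety point about wording that can be corrected cheaply.

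**What to change.** Change item 27 in three ways:

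- Delete the statement that listed deviations are due to surgery and not induced by the study protocol.
- Fix the exception list and the plausibility list, with a date, before the first patient is enrolled. State that they waive the 24-hour notification and nothing else.
- Require every listed deviation to be entered in the case report form in all three arms, without presuming its cause, so that it can be counted by arm. The layout of that count can be left to the analysis plan.

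The cost is an edit to item 27, a few fields on the paper form, and a little more recording. No treatment rule, endpoint or sample size changes.

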**Appendix 1:**

**Selection of relevant outcome studies using the Oesophageal doppler:**

| **Study** | **n-number**  **ASA-Status** | **Surgical specialty** | **Patient outcomes** |
| --- | --- | --- | --- |
| Mythen 1995 | 60  ASA III | Cardiac surgery | No increase in morbidity  41% reduction in ICU care  37% reduction in hospital care |
| Sinclair 1997 | 40  ASA II/III | Hip fractures  Traumatology | 39% reduction in hospital care |
| Gan 1999 | 44 | Urology/  Gynaecology | 33% reduction in hospital care |
| Venn 2002 | 90  ASA III/IV | Hip fractures  Traumatology | 44% reduction in time till medically fit  23% reduction in hospital care |
| McKendry 2000 | 39 | Cardiac surgery | 19% reduction in hospital care |
| Gan 2002 | 100  ASA I/II/III | Urology/  Gynaecology | 29% reduction in hospital care |
| Wakeling 2005 | 134  ASA I-III | Abdominal  surgery | 37 % reduction in patient complications  13 % reduction in hospital care |
| Noblett 2006 | 108 | Abdominal-surgery | 22 % reduction in hospital care  Reduction in life-threatening complications |

**Abbreviations:**

ASA American Society of Anesthesiologists

ICU Intensive care unit

**Appendix 2:**

|  | | | **Differences to control method** | | | **Limits of Agreement** | |
| --- | --- | --- | --- | --- | --- | --- | --- |
| **Studies and control method** | **No. Pat.** | **No.**  **Obs.** | **Bias**  **L/min** | **Precision**  **L/min** | **95% Co.-In.**  **L/min & %** | **Upper**  **L/min** | **Lower**  **L/min** |
| de Wilde et al.  Cardiac surgery, intra-op.  CO-thermodilution | 27  88 | 199  301 | -0.17  -0.02 | 0.69  0.65 | 1.38 (28.6%)  1.3 (25.7%) | -1.55  -1.28 | 1.20  1.32 |
| Missant et al.  Cardiac surgery, intra-op.  CO-thermodilution | 20 | 149 | -0.03 | 0.65 | 1.3  (29%) | -1.33 | 1.26 |
| Costa et al.  Liver tranpslantation, post-op.  CO-thermodilution | 23 | 151 | 0.29 | 1.09 | 2.17  (16.8%) | -1.87 | 2.46 |
| Kim et al.  Pediatric intensive care unit (*: cardiac index)  CO-thermodilution | 20 | 73 | 0.19* | 0.14* | 0.28*  (8.5%) | -0.09* | 0.47* |
| Pittman et al.  Intensive care unit (24 hrs.)  Lithium-thermodilution | 21 | 83 | -0.01 | 0.82 | 1.64  (27%) | -1.65 | 1.63 |
| Hamilton et al.  Cardiac surgery, post-op.  Lithium-thermodilution | 20 | 80 | 0.1 | 0.6 | 1.2  (21.8%) | -1.1 | 1.3 |

**Abbreviations:**

No. Number

Pat. Patients

Obs. Exams

Ko.-In. Confidence-Intervall

**Appendix 3:**

**Algorithm for the goal-directed volume and catecholamine therapy of the intervention groups**

*: The stroke volume after the initial preload-optimization is the Starting-SVI.

#: The drop of the stroke volume index is related to the Starting-SVI.

x: Are there clinical (a opinion of the surgeon in combination with the estimation of the anaesthesists) or haemodynamically (in the form of an elevated central-venous pressure in combination with the clinical estimation) sign for a backward failure of the right ventricle to the liver, the administration of enoximone (initial dosis: 2,5µg/kg/min, can be increased up to 10µg/kg/min or a bolus administration of 1µg/kg) or nitroglycerine should be indicated according to the clinical estimation of the anaesthesists in charge. The simultaneous administration of both drugs must not be indicated in the same patient due to the risk of hypotension.

**Abbreviations of the diagram:**

SVI Stroke volume index

SBP Systolic arterial blood pressure

MAP Mean arterial blood pressure

**Appendix 4**

**Definition of infectious complications:**

For the diagnosis of an infection the following SOP from our hospital will be applied in accordance with the CDC criteria and ATS guidelines [15]:

**Pneumonia:**

In this case one of the following criteria must be fulfilled:

**Crackles on auscultation or dullness to percussion**

and one of the following signs:

- Newly developed purulent sputum or a change in its characteristics,
- Microbes isolated from blood cultures.
- Pathogen isolated from bronchoalveolärer lavage, bronchial swab, transtracheal aspirate or biopsy sample

**Chest x-ray demonstrating new or progressive infiltrates, opacification, cavitation or a pleural effusion.**

and one of the following signs:

- Newly developed purulent sputum or a change in its characteristics,
- Microbes isolated from blood cultures.
- Pathogen isolated from bronchoalveolärer lavage, bronchial swab, transtracheal aspirate or biopsy sample

**Tracheobronchitis:**

2 of the following criteria must be met without signs of pneumonia:

- Fever (38°C)
- Cough
- New or increased sputum production
- Dry crackles

and **one** of the following criteria must be met:

- Microrganisms isolated through culturing tracheal secretions or material obtained via bronchoalveolar lavage.
- Positve antigen-test from the airway

**Wound infection:**

**Superficial post-operative wound infection:**

Infection at the incision site within 30 days of operation which only involves the skin or subcutaneous tissues,

and one of the following criteria are met:

- Purulent discharge from the superficial incision
- Microbe isolated from culture of an aseptically obtained wound secretion or a tissue culture of the superficial incision

and one of the following signs:

- Pain
- Tenderness
- localised swelling
- Erythema or warmth
- The surgeon would open the superficial incision except that a **negative culture exists before the diagnostic decision**.

**Deep post-operative wound infection:**

Infection within 30 days of operation. The infection appears to be associated with the operation and involves muscle tissue and fascial layers.

In addition to this one of the following criteria must be met:

- Purulent secretions from deep in the incision but not from an organ and/or body cavity
- Spontaneous drainage or deliberate surgical incision when the patient has at least one of the following symptoms:
- Fever (>38°C)
  - localised pain or tenderness
  - culture is confirmed negative
- An abscess or other sign of infection is evident from clinical, radiological or histopathological examinations or during re-operation
- diagnosis made by the surgeon

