| 4.Subject of the study and its aims  (Hypothesis divided into primary and secondary hypotheses) | Primary Hypothesis:  Compared to conventional therapy an intra-operative goal-directed haemodynamic management by monitoring with LiDCOrapid or oesophageal Doppler improves haemodynamics measured by stroke volume (SV) in patients undergoing elective liver resection.  Secondary hypothesis 1:  Compared to conventional therapy an intra-operative goal-directed haemodynamic management by monitoring with LiDCOrapid or oesophageal Doppler reduces the incidence of perioperative dysfunction (cerebral, pulmonary, renal, abdominal and cardiovascular), the amount of intraoperative blood loss and the postoperative incidence of infections and quality of life in patients undergoing elective liver resection.  Secondary hypothesis 2:  Compared to conventional therapy an intra-operative goal-directed haemodynamic management by monitoring with LiDCOrapid or oesophageal Doppler the postoperative liver function in patients undergoing elective liver resection.  Study groups:  The administration of the volume and catecholamine therapy is carried out by:  1.) Conventional standard therapy  2.) Goal-directed haemodynamic management by monitoring with oesophageal Doppler  3.) Goal-directed haemodynamic management by monitoring with LiDCOrapid  Primary outcome measure:  Stroke volume before intra-operative start of liver resection  Secondary outcome measures:   - Intra-operative and post-operative haemodynamic parameters - Intra-operative and post-operative blood loss - frequency of organ dysfunctions (cerebral, pulmonal, renal, abdominal, cardiovascular) - Post-operative liver function (LiMAx-test, ICG-Clearance, liver Doppler, laboratory tests: enzymatic and chemical parameters) - Peri-operative weight change - Post-operative incidence of infections - Satisfaction of the patients, the surgeons and anaesthetists - Time to fulfilling discharge criteria - Length of intensive care stay and hospital stay (LOS) - Quality of life measure (EQ-5D) - Laboratory tests: peri-operative endothelial and immunological alterations |

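### Appendix 4 has no category for organ or body-cavity infection, so an intra-abdominal infection after liver resection is captured only through sepsis or muscle-and-fascia involvement

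*Protocol*

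**What the plan says.** Protocol item 4 lists infection after surgery among the secondary outcome measures, and secondary hypothesis 1 expects goal-directed management to reduce the "postoperative incidence of infections". Appendix 4 then sets the diagnostic rule: "For the diagnosis of an infection the following SOP from our hospital will be applied in accordance with the CDC criteria and ATS guidelines".

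The site-specific entries that follow are pneumonia, tracheobronchitis, superficial and deep wound infection, urinary tract infection and sinusitis. SIRS, sepsis, severe sepsis and septic shock come next, and then ARDS and the Lung Injury Score.

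The two wound entries are bounded by tissue layer:
- Superficial: "Infection at the incision site within 30 days of operation which only involves the skin or subcutaneous tissues".
- Deep: "The infection appears to be associated with the operation and involves muscle tissue and fascial layers". One of several further criteria must be met in addition. The first is "Purulent secretions from deep in the incision but not from an organ and/or body cavity". Others are "An abscess or other sign of infection is evident from clinical, radiological or histopathological examinations or during re-operation" and "diagnosis made by the surgeon".

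**The concern.** Every patient in this trial has a liver resection, so the abdominal cavity and the resection surface are the operative field. The deep-wound pus criterion deliberately sets organ and cavity pus apart from incisional pus, which makes sense only if another entry receives it. Appendix 4 has no such entry.

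What is at stake is the completeness and consistency of a named secondary outcome. An assessor with an infected collection at the resection surface has three options: leave it out, stretch the deep-wound entry to hold it, or record it as sepsis if the systemic criteria happen to be met. Different assessors may choose differently. Item 15 says that the results are to lead to a later randomised study with a calculated sample size, so an incomplete infection rate could carry over into that planning.

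**Working it through.** The plan states no infection rate, so there is no figure to reproduce. The check is one of coverage: take an intra-abdominal infection after liver resection and try each entry in Appendix 4.

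1. **Pneumonia, tracheobronchitis, urinary tract infection, sinusitis.** These concern other sites and do not apply.
2. **Superficial wound infection.** Restricted to skin and subcutaneous tissue. Does not apply.
3. **Deep wound infection, pus criterion.** Organ and cavity pus is excluded in terms. Does not apply.
4. **Deep wound infection, abscess or surgeon's diagnosis.** Neither criterion repeats the cavity exclusion, and one criterion is enough. Both, however, come in addition to the entry condition of muscle and fascial involvement. They apply only when the abdominal wall layers are involved too. A collection confined to the cavity or the resection surface does not qualify.
5. **Sepsis and its severe forms.** Sepsis needs SIRS plus an infection that is documented or suspected, with no restriction by site. This applies whenever SIRS is present. None of the site entries in steps 1 to 4 requires SIRS, so an abdominal infection faces a condition that the other sites do not. The entry also does not record where the infection was.

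Result: no site-specific entry names an organ or cavity infection, one route is independent of site (sepsis), and one is conditional (deep wound with muscle and fascia). An intra-abdominal infection without SIRS and without muscle or fascial involvement fits nothing.

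**Which entries form the outcome.** The protocol does not say. All of Appendix 4 cannot be meant, because it also holds ARDS and the Lung Injury Score, which are not infections. Whether sepsis counts towards the incidence of infections is therefore open, and so is the main alternative route.

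**Illustration of size.** The group size of 20 (60 in total) is from item 14. The rate of organ or cavity infection is an assumption of 5-15%.
- Per arm: 20 × 0.05 = 1 and 20 × 0.15 = 3.
- Whole trial: 60 × 0.05 = 3 and 60 × 0.15 = 9.

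These are ceilings, since they suppose that no such patient is picked up through steps 4 or 5. If half met the sepsis definition, again an assumption, and sepsis were counted, the number missed would be 0.5 × 1 = 0.5 to 0.5 × 3 = 1.5 per arm.

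**Time window.** Both wound entries use 30 days from operation. Items 23 and 27 end monitoring at discharge or day 8, whichever is earlier. Item 12 gives discharge or 30 days. The observation period behind the 30-day definitions is therefore not settled.

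**The case against.** The strongest reply is that these infections are not shut out. The SIRS thresholds are modest (for example temperature above 38 °C together with heart rate above 90/min), and many patients with an infected collection would meet two of them and so count as septic. The cavity exclusion sits in a single criterion, and the abscess and surgeon's-diagnosis criteria do not repeat it. The appendix claims accordance with the CDC criteria, and the make-up of the outcome may be stated in a case report form or analysis plan that is not shown.

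Much of this stands. A reader might infer from the exclusion that intra-abdominal infection is never counted. The documents do not support that, because sepsis takes in infection at any site and some cases can properly enter as deep wound infection. What the reply does not do is close the gap for the patient without SIRS whose infection spares muscle and fascia. The reference to the CDC criteria adds no category to the list, and the definitions themselves are fixed in this protocol, not deferred.

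Three further inferences should be resisted:
- That the comparison between arms is biased. All three arms use the same definitions, and the documents show no mechanism for differential miscounting.
- That the omitted site is tied to the trial's mechanism. Item 5 discusses splanchnic perfusion but does not link it to infection.
- That a given share of all infections is lost. The protocol gives neither a total infection rate nor a rate by site.

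**Conclusion.** The point holds as a gap in coverage. Appendix 4 separates organ and cavity pus from wound infection and gives it no entry of its own, so after liver resection an intra-abdominal infection is captured only with SIRS or with muscle and fascial involvement. The secondary infection outcome is incomplete and open to inconsistent classification.

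The size of the undercount cannot be determined from the documents. The figure of at most 1-3 of 20 per arm rests wholly on the assumed 5-15% rate and on no case entering by another route. Infection is one of many secondary outcomes in a 60-patient pilot whose p values item 15 calls exploratory, and the primary stroke-volume analysis is not affected. The change is worth making because the gap concerns the operative field and is cheap to close.

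**What to change.** - Add an organ/body-cavity infection entry to Appendix 4 and count it in the infection outcome. Suitable criteria would be pus from an intra-abdominal drain or collection, a positive culture obtained from it aseptically, or an abscess seen on imaging or at re-operation.
- List the Appendix 4 entries that make up the infection outcome, and say whether sepsis is one of them.
- Reconcile the 30-day window in the wound entries with the follow-up in items 23 and 27 (discharge or day 8) and in item 12 (discharge or 30 days), so that the new entry and the existing wound entries can be ascertained over the period they name.

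The new entry can be read from routine clinical, imaging and microbiology records and needs no extra procedure. The cost is one more item to adjudicate. Settling the window may also lengthen the period over which records have to be read, depending on how it is resolved.
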